## Abstract

Physical activity during pregnancy assumes an important role in the health of both the pregnant and newborn. Given that physical activity tends to decrease throughout this period, it is essential to inform and encourage pregnant women to acquire healthy lifestyles, enabling them to improve their physical and psychological well-being.

This study aims to evaluate the impact of an intervention program on pregnant, newborn, and gestation outcomes, by increasing physical activity levels during this important period of woman's life.

This study will be conducted with 410 pregnant women in the first trimester. Participants will be recruited through the central hospital or community centers. Following consent and baseline data collection, pregnant women who do not have any medical or obstetric contraindication for physical exercise, will be assigned to the control or intervention groups. There will be 3 assessment periods: baseline (time 1—between the 7th and 10th week of gestation), after the intervention (time 2—between the 1st and 3rd day after delivery), and follow-up (time 3—1 month after delivery). The intervention group will have an intervention program, which comprises 2 terms: (1) teachers’ training delivered by researchers and (2) intervention delivered to pregnant women by trained teachers, which consists in 3 weekly classes of physical exercise (45/50 min each). The control group will have the standard care that is usually provided by health professionals.

The research has been approved by the Subcommittee on Ethics for the Life Sciences and Health of the University of Minho (id: SECVS 086/2015) and by the Ethics Committee for Health from the Central Hospital (id: 056/2014). There is a registration in clinical trials.gov, with the reference NCT03045237 (02/2017).

This study has the potential to increase pregnant's physical activity levels and contribute to programs and policies developed to optimize lifestyles during pregnancy and with implications in newborn outcomes.

## Introduction

Experts have not always been favorable in relation to physical activity (PA) during pregnancy. Nonetheless, nowadays engaging in regular PA is considered an important determinant to improve maternal and neonatal outcomes.^1–3^

For a healthy pregnancy, it is recommended to improve healthy lifestyles, namely, daily PA and a balanced diet, essential for the well-being of both pregnant women and newborn. The American College of Obstetricians and Gynecologists^4^ recognizes the benefits of PA and, unless medical or obstetrical contraindications, recommends that all pregnant women are encouraged to be active at least 30 minutes on most of the days. Sedentary women should start with moderate intensity exercise, a minimum of 15 minutes 3 to 4 times a week, then increasing to 30 minutes 5 times a week.^5^

It is recognized that the lifestyle and habits adopted during pregnancy can affect women's health for the rest of life: control of weight gain, maintenance or improvement of physical capacity,^6^ and the conditions of placental irrigation, tone the muscles most affected during pregnancy (such as pelvic muscles, abdominal area, or lower back)^7^ and helps in postpartum recovery.^8^ Regarding the delivery, PA may decrease its duration and the need for epidural,^8^ in addition to a reduction in the number of births by caesarean section.^9^ The increase in exercise level before, during, and after pregnancy contributes positively in the prevention and treatment of several diseases such as pre-eclampsia,^10^ urinary incontinence,^7^ gestational diabetes,^11,12^ low back pain,^13^ and preterm birth.^11^ For symptoms of depression such as mood, insomnia, and anxiety, most studies point toward an improvement of these complaints, in combination with a better general condition and a more energetic and optimistic attitude.^14^

PA also influences the health of the newborn^6^ by improving the Apgar score at first and fifth minutes,^4^ and the intrauterine environment modulations, which will influence the fetal development and consequently child's life.^15^ By helping with control of the gestational weight gain,^16^ it also reduce the risk of macrossomia, chronic conditions, and birth defects.

Despite all benefits described previously, it is well known that the level of PA decreases since the beginning of pregnancy,^17^ whether PA is performed at work and/or leisure.^18^ This fact is confirmed in the study of Currie et al,^19^ which indicates that the moderate and vigorous PA declined the most between the second and third trimester.

Until now, there are few intervention programs developed and implemented during pregnancy. Therefore, we will develop the intervention program “Healthy Bellies,” a partnership between University of Minho, local Hospital, and the City Hall.

The study aims to evaluate the impact of an intervention program, based on the promotion of PA, on pregnant, birth, and newborn outcomes. We hypothesize that the compliance to the intervention program is associated to a reduced (1) gestational weight gain and weight retention postpartum and (2) depressive symptoms. In addition, the intervention program will benefit the delivery (type, duration, complications) and improve infant's birth weight and length.

## Methods

### Recruitment

In the hospital, during the first trimester biochemical screening (between the 7th and 10th week of gestation), 410 pregnant women will be invited to participate in this quasiexperimental study. Participants who want to engage in the PA program will be assigned to the intervention group after the 12th week and the others will be included in the control group, following the standard care procedures provided by health professionals in Portugal (205 women in each group).

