### Sample size

For sample size estimation we will use the variable of interest PA intensity in METs/h/wk. In Portugal, the PA average in pregnant is 210.35 ± 116.75 METs/h/wk.^28^ To detect 20% difference in PA between groups in the third trimester (increasing average PA in intervention group by ≈42 METs/h/wk), with type I and II errors of 5% and 20%, we will have an effect size of 0.36. A sample of 244 pregnant women (122 in each intervention and control group) is anticipated to stage 3. Assuming a dropout of 30%, we propose a sample size by stage 1 of 318 pregnant women, 159 per group; Fig. 1).

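### The protocol gives two enrolment targets, 410 and 318; neither follows from its own inputs, and 318 is too small for the stated 30% dropout

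*Protocol article*

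**What the plan says.** Three places in the protocol article give the size of the study.

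- **Abstract:** "This study will be conducted with 410 pregnant women in the first trimester". No group size is given there.
- **Methods, Recruitment:** "410 pregnant women will be invited to participate in this quasiexperimental study", with "205 women in each group". Group is set by the woman's own preference: "Participants who want to engage in the PA program will be assigned to the intervention group after the 12th week and the others will be" controls under standard care.
- **Methods, Sample size:** "A sample of 244 pregnant women (122 in each intervention and control group) is anticipated to stage 3". After an allowance for 30% dropout, "we propose a sample size by stage 1 of 318 pregnant women, 159 per group".

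The inputs to the calculation are also in the Sample size section: "the PA average in pregnant is 210.35 ± 116.75 METs/h/wk", a 20% difference of about 42 in the same units, type I and II errors of 5% and 20%, and an effect size of 0.36.

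**The concern.** Outcome measures defines stage 1 as the start of the programme, so 318 is a number of women enrolled. Recruitment allocates 205 women to each group, so 410 is also a number of women in the study. The two differ by 410 - 318 = 92 women, or 46 per group, and the text does not account for the gap.

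A team working from this article cannot tell which number ends recruitment, or whether 410 counts invitations or participants. The choice also affects power. If the smaller number is used and dropout really is 30%, the study ends below its own planned power.

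**Working it through.** **Inputs (Sample size section).** SD 116.75; difference 42; alpha 0.05; power 80%; dropout 30%. Whether the test is one- or two-sided is not stated.

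**1. Reproduce the stage 3 figure.**
- Effect size: d = 42/116.75 = 0.36.
- n per group = 2(1.96 + 0.84)²/d². This gives just over 121, rounded up to 122. The t-test version at d = 0.36 gives 122.1.
- A one-sided test would need only 96 per group, so the plan's figure is two-sided.
- The stated 122 per group (244) is confirmed.

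**2. Allow for 30% dropout.**
- To keep 122 after losing 30%, enrol 122/(1 - 0.30) = 174.3, so 175 per group, 350 in total.
- The plan's 159 is 122 x 1.3 = 158.6. This adds 30% of the final number instead of dividing by the fraction retained. It covers a loss of only 1 - 122/159 = 23.3%.
- 205 comes from neither form. Going from 205 to 122 implies a loss of 1 - 122/205 = 40.5%.

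**3. Power after 30% loss** (two-sided t-test, d = 0.36, equal groups, same loss in both groups).

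| Enrolled per group | Left after 30% loss | Power |
|---|---|---|
| 159 | 111 | 76% |
| 175 | 122 | 80% |
| 205 | 143 | 86% |

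**4. Does inviting 410 give 205 per group?** Only if every invited woman consents, every one is eligible (Participants requires a medical attestation), and exactly half choose the programme. This is possible, but the allocation method described does not produce it. The rule that a woman must complete at least 10 classes to count in the intervention group makes it less likely.

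**5. Effect of unequal uptake.** The documents give no uptake rate, so the rates below are assumptions. All 410 are taken to enrol, with 30% loss in each group.

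| Choosing the programme | Enrolled | Power |
|---|---|---|
| 50% | 205 v 205 | 86% |
| 40% | 164 v 246 | 85% |
| 30% | 123 v 287 | 79% to 80% |
| 20% | 82 v 328 | 68% to 69% |

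Ranges reflect the t-test and the normal approximation. For 30% uptake, 86 v 201 remain, and the t-test gives 79.5%.

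**The case against.** The best defence is that 410 counts women approached and 318 counts women enrolled. That would be an ordinary allowance for refusals, with 318/410 = 77.6% joining. It fails on the text, because Recruitment places 205 women in each group and the Abstract says the study is conducted with 410. Figure 1, cited beside the 159, is not shown and might carry linking counts. The statement that nothing derives 410 is therefore safe only for the visible text. Even so, a figure could not make group sizes of 205 and 159 agree.

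Three further objections stand and limit the point.

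- A reader might infer that equal groups of 205 are impossible when women choose for themselves. The documents do not support that. The 205 can be read as a planned group size, the Abstract mentions community centres as a second source of participants, and a journal article may leave the way groups are filled to the full protocol. The fair statement is that the equal split is not implied.
- A reader might infer that the 80% power claim collapses under self-selection. With 410 enrolled, power stays close to 80% even at 30% uptake. It falls clearly only near the assumed 20%.
- The 76% at 318 is caused by the dropout inflation and would be there even if 410 were never mentioned.

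**Conclusion.** The point holds in this form: the article states two enrolment targets that do not agree, and neither follows from its stated inputs. The required number is about 175 per group (350). The 318 falls short of it by 32 women and gives about 76% power. The 410 exceeds it by 60 and gives about 86% if the groups are equal. Using 410 both for invitations and for two equal groups is a looseness of wording to correct, not a demonstrated loss of power.

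These figures assume a two-sided comparison of two means, the stated SD and difference, and 30% loss in each group. The Discussion expects more dropout among controls, which would change them somewhat. The results for unequal uptake rest on assumed rates and serve only as illustration.

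**What to change.** State one target in the Abstract, Recruitment and Sample size sections, as women enrolled at stage 1, and correct the dropout calculation to 122/0.7, at least 175 per group (350 in total).

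If the 205 per group already planned is kept:
- delete 318 and 159;
- say that 205 exceeds the minimum of 175, leaves about 143 per group after 30% loss, and gives about 86% power with equal groups;
- say that 205 per group is a target for women enrolled and not the result of inviting 410;
- say that power will be lower if self-selection gives unequal groups, for example about 79% with 410 enrolled if 30% choose the programme, marked as an assumed rate.

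The change is mostly to text. Its real cost is that the number of women invited is no longer fixed at 410, so more may have to be approached and recruitment may take longer. Any linking counts in Figure 1 should be brought into line.

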### Outcome measures

Data will be collected in 3 stages: (1) at the beginning of the program, (2) between first and third day after delivery, and (3) 1 month after delivery.

At baseline (stage 1), information about the sociodemographic profile will be collected, as well as medical history, eating and PA habits, symptoms of depression, and anthropometry. At stage 2, depressive symptoms, PA habits, childbirth information, and anthropometric data of the mother and the newborn will be gathered. At stage 3, depressive symptoms, PA, and food habits of the mother as well as anthropometric data of mother and newborn will be collected.

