### Childbirth data

These data will be collected in the hospital through the analysis of the clinical information, including Apgar index, admission in neonatal care unit, neonatal morbidity, pregnancy complications (hypertensive disorders, gestational diabetes, preterm delivery, and other complications) gestation age at the delivery, labor onset (spontaneous or induced), labor duration and evolution, way of delivery, third and fourth grade perineal lacerations, epidural analgesia, and episiotomy will also be gathered in the hospital through analysis of clinical process.

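### Group membership is settled only after the common week 7–10 baseline, and the article gives two conflicting timings for stage 1

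*Protocol article*

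**What the plan says.** **Recruitment and baseline.** Recruitment (Methods) approaches women "during the first trimester biochemical screening (between the 7th and 10th week of gestation), 410 pregnant women will be invited to participate". The Abstract gives the same window for the first assessment, "baseline (time 1—between the 7th and 10th week of gestation", without distinguishing the groups. It puts assignment afterwards: "Following consent and baseline data collection, pregnant women who do not have any medical or obstetric contraindication for physical exercise, will be assigned" to one of the two groups.

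**Assignment.** Recruitment then says "Participants who want to engage in the PA program will be assigned to the intervention group after the 12th week and the others will be" controls under standard care. Only the intervention side has a date. It is an earliest date, with no latest one.

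**Stage 1.** Outcome measures words the timing differently: "Data will be collected in 3 stages: (1) at the beginning of the program, (2) between first and third day after delivery". Stage 1 includes physical activity habits and depressive symptoms.

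**Outcomes and analysis.** Childbirth data lists "pregnancy complications (hypertensive disorders, gestational diabetes, preterm delivery, and other complications") among the items taken from hospital records. Statistical analysis compares baseline with endpoints between the groups by multivariate regression. The Introduction states that activity declines from the start of pregnancy.

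**The concern.** In a non-randomised comparison, the groups should be formed by what is known at the point from which outcomes are counted. Here baseline comes first, and membership follows from a choice acted on weeks later.

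A woman who develops a complication or a contraindication in between may be unable to join. Read literally, Recruitment then leaves her with the remaining women, who are the controls. The programme group is selected on having reached entry in good order, and no such condition is stated for the control group. Adjusting for baseline covariates does not repair this, because the selection happens after baseline.

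The stage 1 wording raises a second problem. If intervention women are measured when their programme starts and controls at weeks 7–10, the two baselines sit at different gestational ages. Part of any difference in change is then a gestational-age effect. Physical activity is affected most directly, and it is also the variable on which the sample size rests.

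**Working it through.** The article gives no figure for this gap, so there is nothing of its own to reproduce. The check is week arithmetic, an illustration with assumed risks, and a short derivation for the baseline.

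**1. Time that programme membership requires.**
- Inputs: baseline at weeks 7–10 (Abstract, Recruitment); earliest assignment after week 12 (Recruitment).
- Formula: required time = entry week − baseline week.
- Earliest entry: 12 − 10 = 2 weeks to 12 − 7 = 5 weeks.
- Later entry is not excluded, but any later week is an assumption. Entry at week 16 gives 6–9 weeks and entry at week 20 gives 10–13 weeks.

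**2. What this could do to an event outcome under no effect.** All risks here are assumed. Let *q* be the risk, between baseline and joining, of an event that both keeps a woman out of the programme and is recorded as an outcome. Let *r* be the later risk, equal in both groups. Equal numbers intend each group (205 in Recruitment; the number cancels).
- Risk in the programme group: *r*.
- Control risk if such women are reclassified as controls: [2*q* + (1 − *q*)*r*] / (1 + *q*).
- Control risk if such women are instead dropped from the study: *q* + (1 − *q*)*r*.
- Worked case, *q* = 2%, *r* = 10%: reclassified, (0.04 + 0.098)/1.02 = 0.1353 and 0.10/0.1353 = 0.74; dropped, 0.02 + 0.098 = 0.118 and 0.10/0.118 = 0.85.

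| *q* (with *r* = 10%) | Spurious risk ratio, reclassified | Spurious risk ratio, dropped |
|---|---|---|
| 1% | 0.85 | 0.92 |
| 2% | 0.74 | 0.85 |
| 5% | 0.54 | 0.69 |

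With *r* from 5% to 15%, the reclassified ratio runs from 0.73 to 0.90 at *q* = 1% and from 0.36 to 0.65 at *q* = 5%. As *q* approaches zero the ratio approaches 1. The direction is fixed; the size depends wholly on *q* and *r*.

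**3. Baseline activity.** Let *d* be the fall in activity between weeks 7–10 and programme start.
- If only intervention women are measured at programme start, their baseline is lower by *d*.
- A comparison of changes from baseline then shifts by +*d* in favour of the programme.
- A regression of the endpoint on baseline with slope *b* shifts by +*bd*, in the same direction when *b* is positive.
- The article gives no value for *d*. The Introduction also reports that moderate and vigorous activity fell most between the second and third trimesters, so *d* may be small over a gap of 2–5 weeks.

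**4. Weight gain.** Anthropometry takes the difference between end-of-pregnancy and pre-pregnancy weight in both groups. The origin is common, so steps 2 and 3 do not carry over.

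**The case against.** The strongest reply is that the text describes a simple sequence: recruit and measure everyone at weeks 7–10, let women choose, and start classes once week 12 has passed. A closing week is the sort of operational detail that a condensed article leaves to the full protocol. Participants applies the medical attestation and the exclusions to all women, and the Abstract assigns only women without contraindications to either group. The Discussion already concedes that the study is not randomised.

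Much of this is fair, and it rules out several stronger readings that a reader might infer:
- **Different starts of follow-up.** The Abstract and Recruitment give both groups the same recruitment and baseline window. Separate starts would follow only from the stage 1 wording in Outcome measures.
- **Joining at any week, or controls moving across later.** Neither is stated. Both are inferred from the missing upper limit.
- **Early losses counting against controls.** Pregnancy loss is not a named outcome. A woman with an early loss has no delivery data to contribute.
- **Weight gain favouring the programme.** With a common pre-pregnancy origin, this is not established.

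Two things remain. The assignment rule is stated, not omitted: it makes membership depend on behaviour after baseline, puts the remaining women in the control group by default, and does not say that controls' eligibility is checked again at the same gestational age. Conceding non-randomisation does not cover this, since it would persist even if motivation were fully adjusted for. The two timings of stage 1 also differ on the face of the text. The programme wording may be a loose way of saying study start, but it should not be left to interpretation.

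**Conclusion.** The point holds in limited form. Programme membership requires at least 2–5 weeks of ongoing, eligible pregnancy after the shared baseline, and longer if entry is later. No equivalent is stated for controls. The resulting bias favours the programme on complications and preterm delivery. Its size cannot be derived from the documents: the risk ratios above rest on assumed risks and are not estimates. If all women join just after week 12 it is probably small, because few of the listed events arise that early.

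The conflict over stage 1 needs no assumption about late entry. It biases the activity comparison only if the programme-start wording is followed for intervention women while controls are measured at weeks 7–10.

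The minimum of 10 classes in Participants adds a further 10/3 ≈ 3.3 weeks of guaranteed time at three classes a week. That is a separate point and is not needed for this one.

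**What to change.** - In Recruitment, name one gestational landmark at which group assignment closes, with the week left to the investigators. At that landmark, classify every enrolled woman whose pregnancy is ongoing and who still meets the Participants criteria as programme or control by her decision. Apply the same check to both groups.
- Count event outcomes from the landmark in both groups, and treat complications dated before it as baseline characteristics. Analyse each woman in her landmark group whatever she does later. The weight-gain definition need not change.
- In Outcome measures, time stage 1 at weeks 7–10 in both groups, as the Abstract does.

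The cost is protocol wording and one date check per woman. Women with early losses and any late joiners would no longer count in the programme group, so it may be slightly smaller, and late joiners analysed as controls would dilute the contrast a little. The landmark closes only the gap described here; the 10-class condition reopens one after it and has to be dealt with separately.

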### Participants

To be a part of this study, participants will have to accomplish the following criteria: have >18 years old and provide evidence by the medical doctor attesting that there are not any medical or obstetrical contraindications to practice exercise. Exclusion criteria will include pregnant who present absolute or relative contraindications to aerobic exercise during pregnancy according to American College of Obstetricians and Gynecologists guidelines.^4^

It is also required at least the accomplishment of 10 classes so that the participants are included in the intervention group.

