### Overview of the program

The intervention program will be based on Bandura theory, which states that the social environment in which people live is part of life and contributes significantly to human development, adaptation, and behavioral changes. People learn and acquire experiences observing the consequences within their environment, as well as the experiences of the people to whom they live. In this context, it is expected a behavioral change resulting from experiences.

The program comprises 2 terms: (1) teachers’ training delivered by researchers and (2) intervention delivered to pregnant women by trained teachers.

During 5 weeks, 6 teachers of Physical Education from the local center of the city hall will have 10 sessions of training (2 h each session). This training workshop, entitled “Healthy lifestyles in pregnancy,” will include the following information: (i) PA during pregnancy (session 1, 2, and 3); (ii) stages of pregnancy, cares, and recommendations (session 4); (iii) nutrition in pregnancy (session 5); (iv) motor development in the first months of life (session 6); and (v) PA strategies in daily living during pregnancy and postpartum (session 7, 8, 9, and 10). In addition, trained teachers will have a meeting once a month during the period of the intervention with the researchers to discuss and reflect about their intervention with pregnant women.

Participants allocated to the intervention group will perform a PA program, 3 times per week, one of which will be developed in the aquatic environment. Classes will last for 45/50 minutes, divided as follows warm up (7/8 min), fundamental part (30 min), and return to calm (10 min). The exercises performed are of moderate/vigorous intensity, and includes aerobic workout, strength, coordination, and flexibility. The program will include every trimester a session about nutrition developed for pregnant.

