### Statistical analysis

Measures of central tendency and dispersion will be calculated for all variables of interest. Comparisons between the baseline and the endpoints of the 2 groups of the study will be performed using multivariate regression models, to address the influence of the PA program in maternal and neonatal outcomes. The data analysis will be performed using IBM SPSS, Version 23.0 (SPSS Inc, Chicago, IL), with a significance level of 0.05.

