## Discussion

Increasing PA during lifespan, including pregnancy, has been strongly associated with and improvement of health and quality of life. This regular practice provides an improvement in the general health of individuals, with relevant results in cardiorespiratory, metabolic, and functional health.^29^ Although the associations between PA during pregnancy and health are well-defined, a cross-sectional study in China with 1056 pregnant women found that only 11% had a compliance to PA international guidelines of 150 minutes a week.^18^ In Portugal, it is known that there is a tendency to decrease PA during pregnancy.^28^

Knowing that interventions targeting excessive weight gain during pregnancy still remain a major challenge^30^ and that some of the pregnancy outcomes investigated showed conflicting findings,^31^ it is important to find the best practices and policies to improve healthy lifestyles in pregnancy and the postpartum period, with implications beyond the improvement of PA, such as in quality of life and newborn outcomes.

Therefore, programs based on PA, accounting for specific characteristics of the population must be developed, guided by a multidisciplinary team of health and educational professionals, in accordance with international guidelines.

We anticipate limitations for the study. First, this is not a randomized controlled trial and we cannot guarantee that participants in the control group do not do any physical exercise and there are also a higher drop out in the control group at stage 3 due to the lack of contact with these participants during the program.

Phone calls and face-to-face meetings will be made to improve compliance to the intervention program and support the participants’ needs and questions that may arise. These contacts will also be fundamental to reduce drop out at follow-up.

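### The 10-class minimum conditions only the intervention group on attendance after assignment, leaves the fate of low attenders unstated, and adds an avoidable selection bias whose size and sign depend on the outcome

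*Protocol article*

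**What the plan says.** Under Recruitment, the protocol article sets assignment by the woman's own wish: "Participants who want to engage in the PA program will be assigned to the intervention group after the 12th week". Everyone else becomes a control under standard care, with 205 women planned per group. No attendance, health or retention condition is attached to the controls.

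Under Participants, after the eligibility criteria, the article adds: "It is also required at least the accomplishment of 10 classes so that the participants are included in the intervention group".

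Overview of the program gives the class frequency: "Participants allocated to the intervention group will perform a PA program, 3 times per week". Statistical analysis then compares the groups so defined: "Comparisons between the baseline and the endpoints of the 2 groups of the study will be performed using multivariate regression models".

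The article does not say what happens to a woman who is assigned to the programme but attends fewer than 10 classes. It states no as-assigned comparison, and nothing elsewhere cancels the rule. The limitations in the Discussion mention the lack of randomisation, possible exercise among controls and dropout among controls, but not selection by attendance.

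**The concern.** The rule sits among the entry criteria but cannot be known at entry. It is met or failed only after assignment, through events that may be related to the outcomes: new complications, falling mood, loss of motivation. Women with the same events in the control group remain controls.

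The contrast is then no longer between women who took up the programme and women who did not. It is between women who took it up and persisted, and a control group that was not filtered for persistence. For outcomes on which persistent women do better anyway, an inert programme would look beneficial.

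Baseline covariates can adjust in part for who chose the programme. They cannot fully adjust for why some women later stopped, because those reasons arise after baseline. This is also not a detail left to an analysis plan: the article states the rule, and the rule defines one of the two groups in every comparison.

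**Working it through.** **1. Timing, from the article's own figures.** Assignment is after week 12 and classes run 3 times per week. With full attendance, 10 / 3 = 3.3 weeks are needed, so the tenth class falls at about week 15 at the earliest (12 + 3.3 = 15.3). With an assumed one class per week it falls at about week 22 (12 + 10). The condition always follows assignment.

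**2. A binary outcome with no true effect.** The article gives no share of early stoppers and no outcome risk for this purpose, so these values are assumed: overall risk p = 0.08 in both groups, share stopping before class 10 s = 0.20, and risk in stoppers k = 2 times that in stayers.

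- Risk in stayers: q = p / (s·k + 1 − s) = 0.08 / (0.40 + 0.80) = 0.0667.
- Risk in stoppers: 2 × 0.0667 = 0.1333.
- Stoppers dropped: risk ratio = 0.0667 / 0.08 = 0.83.
- Stoppers moved to control, with 205 per group and 0.20 × 205 = 41 stoppers: control risk = (205 × 0.08 + 41 × 0.1333) / 246 = 0.0889. Risk ratio = 0.0667 / 0.0889 = 0.75.

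The ratio depends on s and k, not on p or on the size of two equal groups:

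| s | k | Dropped: 1 / (s·k + 1 − s) | Moved |
|---|---|---|---|
| 0.10 | 1.5 | 0.95 | 0.92 |
| 0.20 | 2 | 0.83 | 0.75 |
| 0.30 | 3 | 0.63 | 0.52 |
| any | 1 | 1.00 | 1.00 |
| 0.20 | 0.5 | 1.11 | 1.20 |

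The last two rows show that the bias vanishes when stoppers carry the same risk as stayers and reverses when they carry less. For the last row, stayers have 1 / 0.9 = 1.111 times p and stoppers 0.556 times p. The moved-to-control risk is (1 + 0.2 × 0.556) / 1.2 = 0.926 times p, and 1.111 / 0.926 = 1.20.

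**3. A continuous outcome with no true effect.** The yardstick is the planning effect under Sample size. With an SD of 116.75 and a difference of about 42 METs/h/wk, 42 / 116.75 = 0.36, which reproduces the article's effect size. At two-sided 5% and 80% power this gives 122 per group, also as stated.

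Assume that attendance and outcome are jointly normal with correlation r, and that the lowest fraction f of attenders is removed from 205 intervention women. The spurious difference in SD units is r·φ(z_f) / (1 − f), where z_f is the normal quantile at f. For f = 0.30 and r = 0.3, it is 0.3 × 0.3477 / 0.70 = 0.149 SD.

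| f | r | Dropped, SD | METs/h/wk | Share of 0.36 | Actual type I error |
|---|---|---|---|---|---|
| 0.10 | 0.1 | 0.02 | 2.3 | 5% | 0.054 |
| 0.40 | 0.2 | 0.13 | 15.0 | 36% | 0.206 |
| 0.30 | 0.3 | 0.15 | 17.4 | 41% | 0.284 |
| 0.30 | 0 | 0 | 0 | 0% | 0.050 |
| 0.30 | −0.2 | −0.10 | −11.6 | −28% | 0.151 |

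If the removed women are moved to control instead, the f = 0.30, r = 0.3 case grows to 0.229 SD (26.8 METs/h/wk). Both f and r are assumed.

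**The case against.** **Direction.** A reader might infer that every group comparison is biased toward the programme. The documents do not support that, because the sign follows the relation between attendance and each outcome. Weight gain is an example. Under Anthropometry it is weight at the end of pregnancy minus weight before pregnancy, with no stated adjustment for gestational length. If women who stop through sickness, or who later deliver early, gain less, removing them raises the intervention mean and works against the programme. This objection stands.

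**Who leaves.** A reader might also infer that early stoppers disappear from the study. The text does not say so; they might equally be counted as controls.

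**Mechanism.** At the timings in the working, preterm delivery itself can hardly cause removal, since class 10 falls at about week 15 to week 22. Only an association between early stopping and later preterm birth could act. Women with an early loss in either group lack most delivery and newborn outcomes, so part of that asymmetry cancels. The Discussion also expects that "there are also a higher drop out in the control group at stage 3", with unknown effect on direction. These points limit the claim but do not remove the asymmetry.

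**No randomisation to protect.** The groups are self-selected and the article says so. That is true, but selection on attendance is a second bias, arises after baseline and can be avoided.

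**The hypothesis is about compliance.** The Introduction says: "We hypothesize that the compliance to the intervention program is associated to a reduced (1) gestational weight gain". This is a partial defence. The same section states the aim as the impact of the programme, and a compliance question can be kept as a secondary analysis.

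**Conclusion.** The concern holds in a limited form. The 10-class rule conditions one group only on behaviour after assignment, and the handling of women who fall short is not stated. Either handling adds a selection bias that baseline adjustment cannot fully remove, on top of the self-selection already acknowledged.

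For outcomes on which adherent or healthier women do better, the bias probably favours the programme. Physical activity is the clearest candidate. For other outcomes it may be nil or reversed. The ratios of 0.83 and 0.75, and a spurious difference of up to about 40% of the planned effect in the moderate continuous scenarios, show what is plausible under the assumed values. They are not estimates for this study, because the documents give neither the share of early stoppers nor their outcomes.

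**What to change.** Replace the sentence under Participants with:

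> All women assigned to the programme after week 12 are followed and analysed in the intervention group regardless of the number of classes attended; the comparison restricted to women with at least 10 classes is a secondary compliance analysis, reported as subject to selection.

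The cost is small provided low attenders are followed from the start. Childbirth and newborn data come from clinical records and maternal weight from the pregnancy book, whatever the attendance, and follow-up contacts are already planned. Questionnaire and accelerometer data on low attenders cannot be recovered later if they are not collected.

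There are two downsides. The main estimate may be diluted by low attenders, and confounding by self-selection remains and still has to be addressed through baseline covariates.

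In the secondary analysis, controls could also be restricted to those still pregnant and free of contraindications at the gestational age when intervention women typically reach class 10. This is optional and more than a wording change. No assessment is planned between baseline and delivery, so it is feasible only where the records already collected show that status.
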